### Outcome assessment/data collection

#### Rakai Community Cohort Study (RCCS)

The mLAKE trial is nested within the RCCS which is conducted by the RHSP. The RCCS is an open, population-based cohort established in 1994 [38]. The RCCS currently surveys individuals aged 15–49 years in 40 agrarian, trading, and fishing communities in and near Rakai District, including the community where the mLAKE trial is being implemented. For all communities, the RCCS conducts a census of households with GPS coordinates recorded and all resident household members enumerated by gender, age, and duration of residence, regardless of whether they are present or absent. After census, the RCCS conducts interviews with consenting participants to assess demographics, sexual behaviors, and HIV service uptake. Data are directly entered using ultra-mobile PCs with pre-coded files and edited in the field for range and consistency checks to allow onsite correction of errors. Blood samples are collected for HIV-related tests and HIV viral load assays of HIV-positive persons. Following the interview, free HIV testing services using a three-rapid-test algorithm and post-test counseling are offered to consenting participants. The RCCS currently conducts its survey of the trial community approximately every 18 months. The existing RCCS research infrastructure allows for efficient assessment of all mLAKE trial outcomes.

#### Consent (adults)

As this is an additive counseling service being offered only to community residents randomized to the intervention arm, consent to receive the counseling service will be obtained orally by the Health Scouts. An oral consent script will be displayed on the mobile phones. Individuals will be informed that declining to receive the intervention will in no way impact their ability to receive usual care and services offered through RHSP. Health Scouts are trained to request consent according to best research practices in a confidential, non-coercive manner.

Participants in the parent RCCS study will follow the established written informed consent procedure for RCCS. The RCCS consent notes potential participation in nested studies, such as this one, allows for collection of blood samples, and allows for linking of RCCS data with available data collected originally for clinical purposes.

#### Assent/consent for minors (ages 15–17 years)

Individuals aged 15–17 years will be asked to provide oral informed assent, and their parents or guardians requested to provide concurrent oral consent. For minors who are emancipated (e.g., married or living independently), we will request oral consent from the minor only per Ugandan guidelines. If assent and consent is obtained as described above, adolescents will be interviewed and counseled in private, without the parent/guardian being present.

#### Data monitoring

Primary responsibility for data monitoring will be assumed by a Data Monitoring Committee (DMC) which will consist of study team members (senior investigators and primary analyst) without any competing interests. The DMC will oversee all data sharing, data integrity, data security, and reporting of analyses of study results. The DMC will have access to the original study database and will guide blinded primary data analyses. Study team members with potential competing interests will not be members of the DMC and will not have access to the original study database which will be kept on password-protected servers in Uganda. Access to any data by study arm and primary study outcomes will not be released until the data and related analyses have been reviewed and approved by the DMC.

#### Access to data

Only DMC members will have access to the original study database which will be kept on a password-protected server in Uganda. Data from this database will be accessible to other investigators upon request through the DMC. After trial completion and publication of primary findings, any data sharing will adhere to established data-sharing policies of RHSP.

### Randomization

#### Eligibility criteria for clusters and participants

All 40 clusters are eligible for randomization (Fig. 1). All cluster residents aged 15 years and older are eligible for participation.

#### Sequence generation, allocation concealment mechanism, and implementation

Given the fixed sample size and desire for baseline comparability of important characteristics, we used restricted randomization to allocate intervention arms [39]. First, we defined a priori that we would accept up to 7.5% difference in baseline cluster level characteristics (including percentage of residents aged 20–29 years in the cluster, percentage of women) and in primary study outcomes (including cluster level percentage of men circumcised, percentage of HIV-positive persons in care, percentage of HIV-positive persons taking ART, percentage HIV PVP). The 7.5% threshold was chosen for simplicity, consistency, and face validity. Second, we conducted 2500 independent, simple, computer-generated randomizations, assigning 20 clusters to one arm (coded as 0) and 20 clusters to a second arm (coded as 1). Third, among the 2500 randomizations, those who did not satisfy the above comparability criteria were removed, resulting in 455 eligible randomizations. Fourth, from the 455 randomizations, one randomization sequence was randomly drawn for allocation of intervention. Final assignment of arms (0 and 1) to intervention and control was done in a public coin-flip ceremony witnessed by study staff and the Health Scouts.

#### Blinding

By nature of the intervention, Health Scouts and participants will not be blinded to intervention assignment. The RCCS study team members assessing outcomes, including the primary analyst, will be blinded to intervention assignment.

### Sample size/power

The sample size for this trial is fixed. Therefore, the relevant study power-related question was to estimate whether the trial had reasonable chance to detect public health-relevant differences in primary study outcomes, i.e., minimum detectable differences (MDD). Baseline data from a mid-2015 RCCS survey of the fishing community were used to first estimate the coefficients of variation (CV) or intracluster correlation coefficients (ICC) (Table 4). We then used prior data from 9–10/2013 (approximately 18 months prior to the mid-2015 data) to project the expected prevalence of the primary outcomes expected for the control arm at the end of the trial (Table 4). The mLAKE trial is planned for approximately 36 months of follow-up, i.e., two RCCS rounds after the baseline 2015 round. The assumption is that 2013 through 2015 were times of rapid scale-up of CHP service access and that this momentum will slow (roughly by 50% for MC, HIV care and by 75% for PVP, ART, and HIV incidence) over the next 36 months.

**Table 4 Tab4:** Power calculation parameters and derivation of control arm outcome estimates at the end of the trial

Characteristics	CV	ICC	2013	2015	2013 to 2015 ∆	Proposed control arm outcome
Population viremia prevalence (PVP)	0.33	0.02	25%	16%	9%	11.2%
HIV care coverage	0.141	0.061	70%	75%	4.8%	80.1%
ART coverage	0.187	0.072	43%	67%	24.6%	79.7%
MC coverage	0.209	0.062	52%	59%	8.1%	66.9%
HIV incidence	0.929	NA	3.34	2.9	0.44	2.7

*ART* antiretroviral therapy, *MC* male circumcision, *NA* not applicable

MDDs were subsequently calculated with 80% power as described by Hayes and Moulton (Table 5) [39]. Potential impact of contamination was also assessed by assuming 10–50% of control arm residents would be influenced by the intervention. Based upon these calculations, the study should have MDD ratios with 80% power to be able to detect a 41% or greater decrease in PVP, 15% or greater increase in HIV care coverage, 20% or greater increase in ART coverage, and 23% or greater increase in MC coverage. Study power was considered reasonable by the study team for all primary outcomes.

**Table 5 Tab5:** Calculation of minimum detectable difference (MDD) for the mHealth Lakefolk Actively Keeping Engaged (mLAKE) trial

Outcome	Control proportion	% Contamination	Control proportion + contamination	Intervention proportion	MDD ratio	MDD difference
PVP	0.112	0	0.112	0.066	0.593	−0.046
PVP	0.112	0.1	0.107	0.063	0.559	−0.049
PVP	0.112	0.2	0.101	0.059	0.524	−0.053
PVP	0.112	0.3	0.095	0.054	0.482	−0.058
PVP	0.112	0.4	0.087	0.048	0.433	−0.064
PVP	0.112	0.5	0.077	0.041	0.37	−0.071
HIV care coverage	0.801	0	0.801	0.92	1.149	0.119
HIV care coverage	0.801	0.1	0.814	0.934	1.147	0.12
HIV care coverage	0.801	0.2	0.831	0.952	1.145	0.121
HIV care coverage	0.801	0.3	0.854	0.976	1.144	0.122
HIV care coverage	0.801	0.4	NA	NA	NA	NA
HIV care coverage	0.801	0.5	NA	NA	NA	NA
ART coverage	0.797	0	0.797	0.952	1.195	0.155
ART coverage	0.797	0.1	0.814	0.971	1.193	0.157
ART coverage	0.797	0.2	0.837	0.997	1.191	0.16
ART coverage	0.797	0.3	NA	NA	NA	NA
ART coverage	0.797	0.4	NA	NA	NA	NA
ART coverage	0.797	0.5	NA	NA	NA	NA
MC coverage	0.669	0	0.669	0.822	1.229	0.153
MC coverage	0.669	0.1	0.686	0.842	1.227	0.156
MC coverage	0.669	0.2	0.709	0.869	1.225	0.16
MC coverage	0.669	0.3	0.739	0.904	1.222	0.164
MC coverage	0.669	0.4	0.783	0.955	1.219	0.172
MC coverage	0.669	0.5	NA	NA	NA	NA
HIV incidence	0.027	0	0.027	0.005	0.201	−0.021
HIV incidence	0.027	0.1	0.025	0.005	0.176	−0.022
HIV incidence	0.027	0.2	0.022	0.004	0.146	−0.023
HIV incidence	0.027	0.3	0.02	0.003	0.116	−0.024
HIV incidence	0.027	0.4	0.017	0.002	0.08	−0.025
HIV incidence	0.027	0.5	0.014	0.001	0.05	−0.025

*ART* antiretroviral therapy*, MC* male circumcision, *NA* not applicable*, PVP* population viremia prevalence

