**Methods/design:**

The Health Scout intervention is being evaluated through a pragmatic, parallel, cluster-randomized controlled trial with an allocation ratio of 1:1. The study setting is a single high-HIV-prevalence fishing community in Rakai, Uganda divided into 40 contiguous neighborhood clusters each containing about 65 households. Twenty clusters received the Health Scout Intervention; 20 clusters received standard of care. The Health Scout intervention is delivered within the community at the household level, targeting all residents aged 15 years or older. The primary programmatic outcomes are self-reported HIV care, antiretroviral therapy, and male circumcision coverage; the primary biologic outcome is population-level HIV viremia prevalence. Follow-up is planned for about 3 years.

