#### Cluster design

The largest of the fishing communities in the region was selected for the mLAKE trial and 40 was chosen as the number of randomization units. There were several reasons for choosing 40 units or clusters. First, we anticipated 10 Health Scouts being deployed, each of whom would initially be allocated the same number of clusters. Some variation in the type of clusters Health Scouts were assigned was desirable to enable more robust analytic inferences on Health Scout effects. Thus, each Health Scout needed to have at least two assigned clusters. As progressively larger number of clusters increased implementation complexity and risk of contamination, we selected 40 clusters, the minimum number needed to assign each Health Scout two clusters.

The 40 clusters were then defined with consideration of implementation logistics, minimizing contamination, and geographic features such as roads, buildings, and the lake shoreline. Specifically, high-resolution satellite images of the community were digitized in ArcGIS 10.3 (ESRI, Redlands, CA, USA). Household GPS locations from a baseline community census conducted in mid-2015 were overlaid on the digitized map and the community was divided into 40 contiguous clusters (Fig. 2) each containing roughly the same number of eligible households and participants. Each cluster was estimated, using census data, to contain approximately 65 households with approximately 1.65 persons aged over 15 years (target population) in each household or approximately 107 potential eligible clients per cluster. Community-based participatory walks with the Health Scouts were conducted to confirm and refine cluster boundaries prior to participant enrollment [33].

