### Control arm description

Household residents in both study arms will have access to standard of care RHSP HIV prevention and treatment services as described in the “Study setting” section above. Health Scouts are not prohibited from interacting with control arm residents but cannot conduct mHealth-supported counseling home visits with residents outside of the intervention clusters.

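### Table 5 measures its MDD columns against two different, unlabelled control proportions, so the contaminated HIV care, ART and MC rows understate the intervention effect needed for 80% power

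*Protocol article*

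**What the plan says.** In the protocol article's section on sample size and power, "MDDs were subsequently calculated with 80% power" for each outcome, and contamination is then introduced: "Potential impact of contamination was also assessed by assuming 10–50% of control arm residents would be influenced by the intervention". Table 5 gives, for each contamination level, the control proportion, the control proportion after contamination, the intervention proportion, an MDD ratio and an MDD difference. Neither the text nor the footnote says which control the last two columns refer to.

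Two rows show the difference in basis:

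- "PVP 0.112 0.5 0.077 0.041 0.37", with a printed difference of −0.071
- "HIV care coverage 0.801 0.3 0.854 0.976 1.144 0.122"

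The text summarises the table at 0% contamination only: "the study should have MDD ratios with 80% power to be able to detect a 41% or greater decrease in PVP", with 15%, 20% and 23% increases for care, ART and MC. It judges power reasonable for all primary outcomes. Cells with no result are marked NA, expanded only as not applicable.

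Contamination is a live issue in this design. The clusters are contiguous within about 2 km², and "Health Scouts are not prohibited from interacting with control arm residents". The same sentence does bar Scouts from app-supported counselling home visits outside the intervention clusters.

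**The concern.** An MDD under contamination should say how large the intervention's true effect has to be for 80% power. Contamination pulls the control arm towards the intervention arm, so that effect has to increase. For PVP it does: the printed ratio moves from 0.593 to 0.37. For the three coverage outcomes the printed ratio moves slightly the other way, towards 1.

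Those three are all of the primary programmatic outcomes, and Table 5 is the article's only quantification of what contamination costs. Someone who reads down the MDD columns would see PVP as sensitive to contamination and coverage as nearly insensitive. Most of that contrast comes from the change of reference. The protocol plans to measure contamination during follow-up, and this is the table against which the measured level would be read.

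**Working it through.** **1. How contamination enters.** With contamination share c, uncontaminated control p0 and intervention proportion p1, the contaminated control is (1 − c)·p0 + c·p1.

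- Care, 30%: 0.7 × 0.801 + 0.3 × 0.976 = 0.8535 (printed 0.854)
- PVP, 50%: 0.5 × 0.112 + 0.5 × 0.041 = 0.0765 (printed 0.077)

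**2. Which control the MDD columns use.** Each cell is p1 − control; p1/control.

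| Row | Printed | Against p0 | Against contaminated control |
|---|---|---|---|
| PVP 50% | −0.071; 0.37 | 0.041 − 0.112 = **−0.071**; 0.366 | 0.041 − 0.077 = −0.036; 0.532 |
| Incidence 40% | −0.025; 0.08 | 0.002 − 0.027 = **−0.025**; 0.074 | 0.002 − 0.017 = −0.015; 0.118 |
| Care 30% | 0.122; 1.144 | 0.976 − 0.801 = 0.175; 1.218 | 0.976 − 0.854 = **0.122**; 1.143 |
| ART 20% | 0.160; 1.191 | 0.997 − 0.797 = 0.200; 1.251 | 0.997 − 0.837 = **0.160**; 1.191 |
| MC 40% | 0.172; 1.219 | 0.955 − 0.669 = 0.286; 1.428 | 0.955 − 0.783 = **0.172**; 1.220 |

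The differences in all 19 contaminated rows with a result follow this pattern to rounding: 5 PVP and 5 incidence rows against p0; 3 care, 2 ART and 4 MC rows against the contaminated control. The incidence ratios are coarse because the proportions have three decimals, so the differences decide there.

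**3. Coverage rows on the PVP basis** (p1/p0; p1 − p0, from the table's own proportions).

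| Outcome | Contamination | Printed | Against p0 |
|---|---|---|---|
| Care | 10% | 1.147; 0.120 | 1.166; 0.133 |
| | 20% | 1.145; 0.121 | 1.189; 0.151 |
| | 30% | 1.144; 0.122 | 1.218; 0.175 |
| ART | 10% | 1.193; 0.157 | 1.218; 0.174 |
| | 20% | 1.191; 0.160 | 1.251; 0.200 |
| MC | 10% | 1.227; 0.156 | 1.259; 0.173 |
| | 20% | 1.225; 0.160 | 1.299; 0.200 |
| | 30% | 1.222; 0.164 | 1.351; 0.235 |
| | 40% | 1.219; 0.172 | 1.428; 0.286 |

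Relative to 0% contamination, the required difference rises by 0.175/0.119 − 1 = 47% (care, 30%), 0.200/0.155 − 1 = 29% (ART, 20%) and 0.286/0.153 − 1 = 87% (MC, 40%).

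**4. The proportions themselves.** The CV-based formula for proportions in a cluster trial is

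clusters per arm = 1 + (z_α/2 + z_β)²·V/(p0 − p1)², with V = p0(1 − p0)/m + p1(1 − p1)/m + k²(p0² + p1²).

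The inputs are 20 clusters per arm ("Twenty clusters received the Health Scout Intervention; 20 clusters received standard of care"), 80% power, and k from Table 4. Neither alpha nor m is stated. With two-sided alpha 0.05 assumed, the 0% rows imply m = 49.1 (PVP), 49.6 (care), 48.8 (ART) and 48.4 (MC). For care at m = 49: V = 0.00325 + 0.00150 + 0.02958 = 0.03434, and 1 + 7.849 × 0.03434/0.119² = 20.03. With m = 50 the contaminated intervention proportions for the four primary outcomes also match to about 0.001. Incidence does not fit m = 49 (0% ratio about 0.15, printed 0.201; about 68 is needed) and is not relied on here.

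**5. The NA cells.** The formula has no solution at or below 100% coverage in exactly these rows: care from 40%, ART from 30%, MC at 50%. Example, care at 40% with p1 = 1: contaminated control 0.6 × 0.801 + 0.4 = 0.8806; V = 0.00215 + 0.019881 × (0.8806² + 1) = 0.03744; 0.1194 × √(19/0.03744) − 1.96 = 0.73, which is power of about 77%. Full coverage in the intervention arm still falls short of 80%.

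**6. Power if the headline effect is the true effect, 20% contamination.** Care at m = 49: contaminated control 0.8 × 0.801 + 0.2 × 0.92 = 0.8248; V = 0.00295 + 0.00150 + 0.03035 = 0.03480; 0.0952 × √(19/0.03480) − 1.96 = 0.26, or about 60%. Across the four outcomes the range is about 60–64%. The article counts "approximately 107 potential eligible clients per cluster"; with m = 107 the figures are about 62–64% for the coverage outcomes and 83% for PVP.

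**The case against.** The nine coverage rows are not miscalculated in themselves: they give the contrast that would be observed between the arms. The same rows show the required intervention proportion climbing (care 0.92 to 0.976, ART 0.952 to 0.997, MC 0.822 to 0.955) and then NA, and the printed MC difference also rises, from 0.153 to 0.172. The uncontaminated control stands in every row, so a careful reader can recover the true effect. No decision hangs on these cells, because the sample size is fixed and 40 clusters were chosen for logistical reasons. All of this stands, and it limits the consequence. It does not make one column with two unlabelled meanings correct.

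A reader might go further and infer any of the following. The document does not support them.

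- *The headline 41/15/20/23% is wrong.* It comes from the 0% rows, where the two references coincide.
- *The protocol presents contamination as costless, or names it as its main threat.* The intervention-proportion column and the NA rows show a cost. The discussion lists contamination first of three limitations without ranking them.
- *A null result will be misread.* The discussion says contamination may reduce power and that monitoring it is critical, and the study monitoring section plans a questionnaire module to measure it.
- *Scouts have unrestricted contact with control residents.* App-supported counselling home visits outside the intervention clusters are ruled out.

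**Conclusion.** The point holds as an inconsistent, unlabelled reference in the two MDD columns of Table 5. Row arithmetic alone establishes it, with no assumption about alpha or cluster size. The contaminated care, ART and MC cells understate the true effect needed for 80% power: at the highest solvable contamination level the printed differences are 0.122, 0.160 and 0.172, where the PVP basis gives 0.175, 0.200 and 0.286.

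The intervention proportions, contaminated controls and 0% headline are correct, and the design and primary analysis do not change. The headline is incomplete rather than wrong, since it holds only without contamination.

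The power-loss figures are illustrative. They assume two-sided alpha 0.05 and a back-solved m of about 49, and for PVP they depend strongly on m (64% at m = 49, 83% at m = 107, both at 20% contamination). They should not be quoted without those conditions.

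**What to change.** 1. Use the uncontaminated control as the one stated reference for the MDD ratio and difference in all outcomes, with the care, ART and MC values from step 3 of the working. Alternatively, print both contrasts under separate labels.
2. Replace NA in the result cells with a statement that 80% power is not attainable: care at 40% or more, ART at 30% or more, MC at 50%.
3. Say that the headline applies at 0% contamination and add the 20% values beside it: PVP 48% decrease (ratio 0.524); care 19%, ART 25% and MC 30% increase.
4. If power at the headline effects is also reported, state the alpha and the m used.

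The cost is recalculation and rewording. The stated MDDs under contamination become less favourable for three of the four primary outcomes; nothing in the conduct of the trial changes.

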### Participant timeline

Participants were recruited beginning September 2015. As shown in the SPIRIT Figure (Fig. 7), participants will be recruited in an ongoing fashion and followed for two rounds of RCCS or approximately 36 months (usually approximately 18 months between rounds). In-migrating participants can be recruited at any time they are encountered by Health Scouts in an intervention cluster during the study period. Participants can also out-migrate or decline participation at any point in time. Process and qualitative evaluations will be conducted during and after the follow-up period. A cost analysis is planned after trial completion.

**Fig. 7 Fig7:**
[figure not shown]
SPIRIT Figure; the mHealth Lakefolk Actively Keeping Engaged (mLAKE) trial schedule of enrollment, interventions, and assessments

### Participant recruitment

mLAKE trial-specific recruitment began with a community-wide sensitization in which community leaders along with RHSP staff informed the community about the mLAKE trial. They explained the randomized nature of the study using locally appropriate examples. This process had been successfully implemented in previous randomized trials and resulted in excellent community support for RHSP research [40]. When the Health Scouts were subsequently deployed, they began recruiting community residents to receive the counseling service as described above. Recruitment for the RCCS will follow usual procedures [21].

### Statistical methods

The comparability of intervention and control arms will be assessed at baseline. Two-sample *t* tests will be used to compare the baseline cluster-level outcomes (individual-level data at baseline are not available for participants absent from the baseline survey). Additionally, participant demographics (age, sex) are known risk factors for the study outcomes, and will be assessed for comparability. If a baseline outcome or demographic variable are significantly different between arms with *p* value ≤ 0.1, adjusted regression analysis on the outcome variables will be conducted adjusting for baseline covariates.

The cluster-level data for study outcomes will be presented by survey and by arm. The primary analysis will be by intent-to-treat and use generalized linear models (GLM) with generalized estimating equation (GEE) to account for within-cluster correlations. Specifically, the logistic model with GEE will be used for binary outcomes (e.g., PVP, MC, ART), and Poisson log-linear model with GEE will be used for the HIV-incidence outcome. Exchangeable correlation structure will be used in the GEE models. Separate analysis will be conducted for each RCCS follow-up survey to assess the shorter- and longer-term effect of the intervention.

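### Baseline adjustment hangs on a p ≤ 0.1 baseline test that the restricted randomization keeps a primary outcome's own imbalance from triggering; prespecified adjustment would be more precise

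*Protocol article*

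**What the plan says.** Two sections of the protocol article bear on this.

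**Randomization (sequence generation).** The investigators decided beforehand that "we would accept up to 7.5% difference in baseline cluster level characteristics". The listed characteristics are given as "including percentage of residents aged 20–29 years in the cluster, percentage of women", and the listed primary outcomes as "cluster level percentage of men circumcised, percentage of HIV-positive persons in care, percentage of HIV-positive persons taking ART, percentage HIV PVP". Of 2500 simple randomizations, "those who did not satisfy the above comparability criteria were removed, resulting in 455 eligible randomizations". Whether 7.5% is relative or in percentage points is not stated.

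**Statistical methods.** Two-sample t "tests will be used to compare the baseline cluster-level outcomes", and age and sex are also checked. The rule is then: "If a baseline outcome or demographic variable are significantly different between arms", with p ≤ 0.1 as the cut-off, "adjusted regression analysis on the outcome variables will be conducted adjusting for baseline covariates". The covariates are not named. The next paragraph defines the primary analysis as an intention-to-treat logistic GEE with exchangeable correlation, and lists no covariates. Nothing says that the restriction variables enter the model whatever the baseline test shows.

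**The concern.** The design stage treats six baseline variables as important enough to discard more than four-fifths of the candidate allocations. The analysis stage then leaves them out unless a significance test on the same kind of variable fires, and the restriction has made that unlikely for the primary outcomes.

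The trigger also asks the wrong question. A p value comparing randomized arms says how unusual an imbalance is. It does not say how strongly the variable predicts the outcome, and that is what decides how much precision adjustment gains. At stake is precision in a trial whose size is fixed at 40 clusters. When allocation is balanced on prognostic variables that the model omits, the standard error also fails to credit the balance, so the test can run below its nominal level.

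**Working it through.** **1. Reproduce the plan's minimum detectable differences.** Inputs are the CVs (k) in Table 4 and the proportions in Table 5 without contamination. Two-sided α = 0.05 is assumed, since it is not stated. The Hayes–Moulton formula is

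c = 1 + (1.96 + 0.84)² × [p0(1−p0)/n + p1(1−p1)/n + k²(p0² + p1²)] / (p0 − p1)².

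The cluster size n behind Table 5 is not stated; back-solving gives 48.4 to 49.6 for all four primary outcomes. With n = 49, c = 20.02 (PVP), 20.03 (care), 19.99 (ART) and 19.97 (MC), against 20 clusters per arm. The published figures reproduce, so n = 49 is used below.

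**2. What the trigger needs and what the restriction allows.** With p the 2015 value in Table 4, the standard error of the baseline difference between arms of 20 clusters is

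SE = √{(2/20) × [(k·p)² + p(1−p)/49]}.

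For care: √{0.1 × [(0.141 × 0.75)² + 0.1875/49]} = √{0.1 × [0.01118 + 0.00383]} = 0.0387. The t test has 38 df, so p ≤ 0.1 needs a difference of at least 1.686 × SE. The relative limit is 0.075 × p.

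| Outcome | SE | Difference needed for p ≤ 0.1 | Relative limit | p value at that limit |
|---|---|---|---|---|
| PVP | 0.0235 | 4.0 points | 1.2 points | 0.61 |
| Care | 0.0387 | 6.5 | 5.6 | 0.16 |
| ART | 0.0450 | 7.6 | 5.0 | 0.27 |
| MC | 0.0449 | 7.6 | 4.4 | 0.33 |

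On the relative reading, no primary outcome can normally reach p ≤ 0.1. On the absolute reading (7.5 points), ART and MC sit at the edge, care has a narrow window, and PVP is hardly restricted.

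**3. Which reading fits the acceptance rate?** Accepted: 455/2500 = 18.2%. Treating the four outcomes as independent and normal, the chance that all fall within limits is 0.390 × 0.853 × 0.736 × 0.676 = 0.166 (relative) or 0.999 × 0.947 × 0.905 × 0.905 = 0.775 (absolute). Simulation of all six variables, with correlation among care, ART and PVP, gives 17–19% and 77–79%. The relative reading fits.

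**4. How often the rule fires (simulation).**

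| | Relative | Absolute | No restriction |
|---|---|---|---|
| A primary outcome's own test | 0–0.5% | ART 1.5%, MC 2%, care 4–5%, PVP 8–9% | 10% |
| Any of the six restricted variables | 10–14% | 30–35% | 43–49% |

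On the relative reading nearly all firing comes from the two demographics. Assuming 45% prevalence, between-cluster CV 0.05 and 107 persons per cluster, SE = √{0.1 × [(0.05 × 0.45)² + 0.2475/107]} = 0.0168. The trigger then needs 2.8 points and the limit is 3.4, so each demographic retains about a 5% chance of firing.

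**5. What the unadjusted default costs.** Relative reading, with a small-sample-corrected sandwich test and an effect set to about 80% power under simple randomization. The correlation ρ between a cluster's baseline and follow-up values is not in the document, so a range is shown. ART was not run at this calibrated effect.

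| ρ | Care | MC | PVP | Size, unadjusted |
|---|---|---|---|---|
| 0.3 | 79.9 → 80.3% | 78.2 → 80.5% | 80.3 → 80.9% | 4.4–5.0% |
| 0.6 | 82.1 → 86.7% | 80.3 → 85.8% | 80.7 → 83.1% | 3.4–4.0% |
| 0.8 | 81.5 → 91.5% | 80.7 → 91.4% | 81.3 → 84.7% | 2.3–2.9% |

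Arrows run from the unadjusted model to one adjusted for the cluster's own baseline outcome. Each power figure rests on 1500 simulated trials, a Monte Carlo error of about √(0.8 × 0.2/1500) = 1 point. Size with adjustment was 4.8–6.1%. Without a small-sample correction, the unadjusted test had size 5.9–6.4%, 4.3–5.1% and 2.9–3.7% at the three correlations.

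**The case against.** Three stronger readings are tempting, and the document does not carry them.

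- **The rule is a dead letter.** It is not. It responds to any baseline outcome or demographic variable, and some restricted variable fires in 10–14% or 30–35% of trials. Unrestricted variables can fire it too: secondary outcomes are not on the restriction list, and age and sex can be coded in other ways. What is rare is firing by a primary outcome's own imbalance.
- **The planned test is over-conservative.** That depends on the correlation and the variance estimator. An uncorrected GEE sandwich test with 40 clusters is somewhat liberal, and this offsets the effect of restriction: size is about 6% at ρ = 0.3 and clearly below 5% only at 0.8. The article names no correction, but an analysis plan not shown may.
- **The primary model is picked from the data.** The text does not say that the adjusted regression replaces the primary GEE. It could equally be supplementary, in which case the primary model is simply always unadjusted.

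It is also fair to say that the unadjusted analysis stays at 78–82% power in these runs, about what was planned, and that a conservative test does not raise false positives. The loss is measured against a better analysis. At ρ = 0.3 it is close to simulation error, and migration in and out of the community over three years could keep the correlation modest. All of this stands. It limits the size of the point but gives no reason to keep a significance trigger.

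**Conclusion.** The point holds as forgone precision and an ill-chosen rule. It is not a claim of invalid inference. The restriction makes it unlikely that imbalance in a primary outcome leads to adjustment for it. When adjustment does occur, it will more often be because of another variable, and the default model ignores the variables on which the design was balanced. The cost is about 0–2 power points at ρ = 0.3, 2–6 at 0.6 and 3–11 at 0.8. With a corrected test, size falls below 5% at moderate to high correlation.

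These figures rest on the assumed ρ, the back-solved cluster size (40–49 persons for care, ART and MC and 49–100 for PVP in the simulations), α = 0.05 and the assumed demographic inputs. The firing rates also depend on how 7.5% is read; the acceptance rate favours the relative reading. Should-fix.

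**What to change.** Delete the p ≤ 0.1 trigger. State that each primary GEE adjusts, regardless of any baseline comparison, for the cluster's mid-2015 value of the same outcome and for age and sex (the demographics used in the restriction), and uses a named small-sample correction. Report the unadjusted model as secondary. Keep the baseline comparison as description only, and say whether 7.5% was relative or absolute. Settle this before outcome data are analysed by arm.

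The cost is small. Cluster-level baseline values were already used for the restriction, so the missing individual baseline data for people absent from that survey are no obstacle. Adjustment uses a few of about 38 between-cluster degrees of freedom. The logistic odds ratio becomes conditional on the covariates, so a marginal (standardized) effect should be reported if the population-level contrast is the one wanted.
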